#### Covariate measures

Sociodemographic and participant-specific factors from both groups will be measured and treated as covariates to describe the population and assess the effectiveness of the intervention. The socioeconomic level (SES) will be estimated with the sociodemographic stratum registry of the National Planning Department (DANE) [86], and other socioeconomic variables, such as parental education, access to technological means, among others, will be evaluated with the Sociodemographic Characterization Questionnaire [87].

### Interventions

#### Experimental group

The experimental group will participate in a training in computational thinking called COGNI-MACHINE, designed by the first author. The intervention comprises 24 sessions; each session will be structured as a workshop and will take place in the computer room of the participating educational institution. The intervention will last 12 weeks, with two sessions per week of 60 min each.

The training workshops will be based on the principles of problem-based learning, and the activities will be designed following the principles of low floor / high ceiling. For the design of the computational thinking intervention, the following sources were taken into account: (1) The recommendations emerging from the results of the previously conducted pilot test [[30], [45]]; (2) A broad review of activities, projects, and courses available to teach computational thinking in school contexts; (3) A systematic review of background and similar studies.

To select the plugged and unplugged activities that would be part of the training, we reviewed: (1) Existing open-access training and existing repositories of unplugged activities; (2) The integrated development environments available to learn to code in blocks; 3) The educational robotics devices available in the market for Colombia. From these reviews, unplugged activities were selected from different sources such as CS Unplugged, code.org, programemos.com, and Mintic's “Coding for kids” [88]. Lessons from courses B, C, and D of the code.org integrated development platform and the Makecode integrated development platform were selected for the block programming activities. For the plugged projects, he selected the micro:bit V2 microprocessor (see Fig. 2), which is a small programmable board designed by the BBC which has several integrated sensors, Bluetooth connection, radio frequency, push buttons, and LED light outputs.

**Fig. 2 fig0002:**
[figure not shown]
micro:bit board V2.

For the plugged educational robotics activities, an Electricfreaks micro:bit-based robotics kit was selected (Fig. 3), which has a Wukong expansion board, motors, servomotors, additional external sensors (lone-following, ultrasound, toilet level), buildable tiles, among other supplies to develop different types of projects with the micro:bit microprocessor.

**Fig. 3 fig0003:**
[figure not shown]
Example of educational robotics projects in micro:bit with the Electricfreaks robotics kit.

Table 6 summarizes the intervention plan, discriminating the intervention phase, the sessions of each phase, the type of activities conducted, and the computational thinking concepts that will be addressed in said sessions based on the proposed framework by Brennan & Resnick [89].

**Table 6 tbl0006:** Summary of intervention sessions.

Sessions	Intervention phase	Activities	CT concepts							
			Sequences	Loops	Parallelism	Events	Conditionals	Operationals	Variables	Functions
1 to 2	Introduction to computational thinking	- Unplugged activities	x							
3 to 8	Introduction to block language programming and practice of computational thinking skills	- Programming animations and games with courses B, C and D from code.org. - Unplugged activities	x	x		x	x			
9 to l6	Solving problems based on computational thinking	- Development of micro:bit projects programmed in makecode. - Plugged projects	x	x	x	x	x	x	x	x
17 to 24	Robótica educativa	- Educational robotics projects with micro:bit	x	x	x	x	x	x	x	x

#### Control group

The control group at TAU will receive the traditional Technology and Computer Science classes 2 hours a week for 12 weeks. In these classes, students will learn to use Microsoft Office applications. After the 12 weeks of intervention, a crossover design will be conducted so that the control group participates in the same intervention as the experimental group and the experimental group participates in the 12 weeks of traditional technology classes.

### Statistical analysis plan

A hypothesis test will be conducted through Mixed Repeated Measures Analysis of Variance (ANOVA MR) with Bonferroni corrections to look at the differences between groups, in which the pre-test, post-test, and follow-up measures will be the factor of repeated measures. (Within-subject) and the difference between the experimental and control groups as the subject factor. The effect size will be measured with partial eta squared. The assumptions of this type of analysis assume a continuous metric-dependent variable with approximately normal distribution and with homoscedasticity in each of the groups.

A multivariate linear regression analysis will also be performed to assess the correlations between cognitive measures and computational thinking. And logistic regressions to analyze binary variables to evaluate the association between the covariates and the results.

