### Sample's size calculation

We estimated the size of the groups based on two criteria: (1). A review of previous studies showed a mean group size of 34.8 participants and a median of 26 in similar studies in children [30]. (2) The G-Power projection suggested a group size of 22 children for a total sample of 44 children. Table 2 contains the parameters for the calculation of the sample.

**Table 2 tbl0002:** Parameters for the size of the groups.

Parameter	Value	Description
Effect size	0,25 – 0,5	Data based on reports from previous studies.
α error confidence level	0,05	
Sample power	0,95	
Number of groups	2	1 experimental group and 1 TAU control group
Number of measures	3	Pretest, posttest, follow-up
Sample size	N= 22 per group	N=44 full sample

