### Recruitment

We evaluated the possible causes of loss from the sample: (1) subjects who did not meet the inclusion factors for the sample, especially the age of the children; (2) dropout rate for this school grade, which is usually around 15%; consequently, for the recruitment we decided to include 4 fifth grade school groups from the same public educational institution in the city of Ibagué, Colombia. Among the four courses, it is expected to convene approximately 100 children, so that the final sample for the analysis has the minimum projected size.

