### Assignment

The intervention will take place in school contexts, and the sessions will be articulated to curricular work in the area of technology; for this reason, it will be necessary to work with naturally constituted school groups. Consequently, the researchers will not individually assign the subjects to the interventions (Experimental and TAU) but will perform cluster randomization. Studies use cluster randomization in circumstances where individual randomization cannot be achieved, so participants are randomized as groups of individuals or clusters [69]. Randomization will be done by an investigator from outside the study who will assign four sealed envelopes (one for each school group) to each intervention.

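### Four whole classes are randomised but the hypothesis test treats children as independent, so the group-by-time test ignores between-class variation in change and its false-positive rate can be well above 5%

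*Protocol article*

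**What the plan says.** The Assignment section of the protocol article states that "the researchers will not individually assign the subjects to the interventions (Experimental and TAU) but will perform cluster randomization", using "four sealed envelopes (one for each school group) to each intervention". Recruitment gives the number of clusters: "we decided to include 4 fifth grade school groups from the same public educational institution". It adds that "it is expected to convene approximately 100 children", and puts dropout for this grade at about 15%.

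The Statistical analysis plan section specifies the test: "A hypothesis test will be conducted through Mixed Repeated Measures Analysis of Variance (ANOVA MR) with Bonferroni corrections". Pre-test, post-test and follow-up form the within-subject factor, and experimental versus control is the between-subject factor. The assumptions listed are a continuous outcome, approximate normality and equal variances. Independence of children is not mentioned.

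On size, the Sample's size calculation section says: "The G-Power projection suggested a group size of 22 children for a total sample of 44 children". Table 2 gives alpha 0.05, power 0.95, two groups, three measures and an effect size of 0.25 to 0.5. Neither Table 2, the covariates section nor the analysis section contains a class effect, an ICC or a design effect. The Discussion names group randomisation as a limitation but draws no consequence for the analysis.

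**The concern.** The word mixed in the stated test refers to one within-child and one between-child factor. It does not mean a random effect for class. The group-by-time effect is therefore judged against variation between children, with 42 degrees of freedom for a two-occasion change score in 44 children. Because classes were allocated, it should be judged against variation between classes, with 2 degrees of freedom for four classes in two arms.

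Children stay in their natural class and are trained in sessions within the school timetable. Change may therefore differ from class to class for reasons unrelated to the programme. If so, the plan as written can report such a difference as an effect of COGNI-MACHINE, with a p-value and confidence interval that do not reflect it. Recruiting more children from the same four classes makes this worse, because the number of independent units stays at four.

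**Working it through.** **Inputs from the article.** Four classes; about 100 children, so 100/4 = 25 per class; 15% loss leaves about 85, or 21 per class; minimum analysed 44, so 44/4 = 11 per class if spread evenly; nominal alpha 0.05.

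**Assumptions.** Two classes per arm (the split is not stated). ICC of the change score 0.01 to 0.20 (not stated).

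**Step 1: reproduce N = 44.** Take the group-by-time test of a repeated-measures ANOVA, with Cohen's f = 0.25 (the article does not name the metric), three measures, and an assumed correlation of 0.5 between measures:

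- noncentrality λ = f² × N × 3 / (1 − 0.5) = 0.0625 × 44 × 3 / 0.5 = 16.5
- degrees of freedom 2 and (44 − 2) × 2 = 84
- power 0.956; N = 42 gives 0.946

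So 44 is reproduced as an individually randomised sample size with no allowance for clustering.

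**Step 2: type I error by formula.** Design effect DE = 1 + (m − 1) × ICC for m children per class; actual alpha ≈ 2 × [1 − Φ(1.96/√DE)]. Example: m = 11, ICC 0.05 gives DE = 1.5, 1.96/√1.5 = 1.60, alpha ≈ 11.0%.

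**Step 3: type I error by simulation.** The pre-test to post-test change is tested between arms with no true effect, first with children as units, then with class means on 2 degrees of freedom. The last column is a separate simulation of the group-by-time term of the stated three-measure ANOVA, with the ICC applied to both the between-child and the within-child variance.

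| Children per class | ICC | DE | Formula | Change test, children as units | Three-measure ANOVA |
|---|---|---|---|---|---|
| 11 | 0.01 | 1.10 | 6.2% | 6.1% | 6.9% |
| 11 | 0.05 | 1.50 | 11.0% | 11.1% | 13.1% |
| 11 | 0.10 | 2.00 | 16.6% | 17.2% | 23.7% |
| 11 | 0.20 | 3.00 | 25.8% | 27.6% | 39.2% |
| 21 | 0.01 | 1.20 | 7.4% | 7.3% | 8.7% |
| 21 | 0.05 | 2.00 | 16.6% | 16.9% | 22.9% |
| 21 | 0.10 | 3.00 | 25.8% | 26.6% | 37.9% |
| 21 | 0.20 | 5.00 | 38.1% | 40.2% | 57.5% |

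The class-level change test gives 5.0% throughout. The change test is the main figure because the Protocol design section applies the third measure to the experimental group only, so pre-test to post-test is the comparison that both arms clearly have.

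**Step 4: stable class differences.** With a constant class difference (ICC 0.10) and no class-by-time variation, the three-measure simulation gives about 5% for the group-by-time term and about 15% to 26% for the group main effect, for 11 to 25 children per class.

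**Step 5: what a valid analysis can deliver.**

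- Critical t is 4.30 on 2 degrees of freedom against 2.02 on 42, a ratio of 2.13.
- Simulated mean interval-width ratio, class-level to child-level, at 11 per class: 1.90 at ICC 0, 2.00 at 0.01, about 2.3 at 0.05, 2.72 at 0.10.
- Power at f = 0.25 from a class-level three-measure analysis (2 and 4 degrees of freedom, λ divided by DE). With 44 children: λ = 16.5, 11.0 and 8.25 at ICC 0, 0.05 and 0.10 give 67%, 51% and 40%. With 84 children: λ = 31.5/2 = 15.75 and 31.5/3 = 10.5 at ICC 0.05 and 0.10 give 65% and 49%.
- Four classes split 2:2 allow 6 allocations, so the smallest two-sided randomisation p is 2/6 = 0.33.

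**The case against.** The strongest reply is that the hypothesis concerns the evolution of executive functions, which is the group-by-time effect. A class that is simply better or worse throughout cancels from it. That is right: a reader might infer that any difference between classes could pass for a treatment effect, and Step 4 shows otherwise. The inflation of this test needs classes to differ in change. That is plausible when each class goes through the 12 weeks together, but the article gives no data on it and does not say who teaches each class.

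Second, no ICC is given, so an unconditional statement that the false-positive rate is far above 5% is not supported. At ICC 0.01 it is only 6% to 9% across the calculations. Nor is class variation shown to be the main source of uncertainty: with 11 per class it makes up 10% of the variance of a class mean at ICC 0.01 and 37% at 0.05. It passes half only from about ICC 0.10, or about 0.05 with 21 per class.

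Third, the ratio 2.13 tempts one to say that valid intervals are at least that much wider. It is a ratio of critical values only. The class-level standard error on 2 degrees of freedom varies greatly, and with 11 per class at ICC 0.05 the width ratio falls below 2.1 in about 45% of runs.

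Two other replies fail. Bonferroni corrections deal with multiple tests, not with correlated children. And this is not detail left to a fuller plan: the article names the test, its factors, its correction and its assumptions, and that test does not match the allocation.

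**Conclusion.** The point holds in conditional form. The stated test does not use the unit that was randomised, and this mismatch needs no ICC to establish. Its effect on the group-by-time test depends on between-class variation in change. At change-score ICCs of 0.05 to 0.10 the real type I error of a nominal 5% test is about 11% to 17% with 11 children per class and 17% to 27% with 21. It is higher for the stated three-measure ANOVA, and modest at ICC 0.01. These figures rest on an assumed ICC range, an assumed 2:2 split and equal class sizes. A 3:1 split would also leave 2 degrees of freedom, with 4 possible allocations and a smallest randomisation p of at least 1/4. The power of 0.95 in Table 2 holds only if children are independent.

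**What to change.** Replace the primary test with one of two analyses:

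- a comparison of baseline-adjusted class means on 2 degrees of freedom; or
- a linear mixed model with random class and class-by-time effects and a small-sample degrees-of-freedom correction such as Kenward-Roger.

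Report the adjusted mean difference with its 95% confidence interval and the estimated ICC. State the allocation ratio of classes to arms. State that p < 0.05 from a child-level ANOVA will not be read as evidence of efficacy. Restate the power in Table 2 with clustering and its assumed ICC.

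The rewording needs no new data, but it has a price. Intervals will typically be about twice as wide or more, power at f = 0.25 with 44 children falls to about 40% to 51% at ICC 0.10 to 0.05, and a class-level randomisation test cannot reach significance. Reanalysis cannot remove the limit of four clusters. Unless more classes can be randomised, the efficacy claim must be scaled back to an estimate with its full uncertainty.

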### Outcome measures

#### Primary outcome measures

To measure the executive functions of children we have selected neuropsychological tests with recognition and reliability studied. Table 4 contains the selected instruments and the rating parameters.

**Table 4 tbl0004:** Description of primary measures.

Variable	Test	Rating Parameters	Authors
Sequential planning	London Tower	Time since start Execution time Number of moves Number of rule violations	Shallice [72]
Visuospatial planning	Porteus maze, BANFE-2 version.	Number of times it traverses. Number of dead ends Execution time	Flores-Lázaro et al. [73]
Auditory-verbal working memory	WISC-V Digit Scale	Number of right answers in direct order, reverse order and increasing order Digit span in forward order Digit span reverse order Digit span increasing order	Wechsler [74]
Visual spatial working memory	Corsi cubes, version WMS-III	Maximum number of elements Number of correct trials	Corsi [75] Wechsler [76]
Visual working memory	WISC-V Span of drawings Scale	Span of drawings Span of stimuli	Wechsler [74]
Cognitive flexibility	M-WCST Wisconsin cards abridged version	Number of right answers Number of maintenance errors Number of perseverations Number of deferred perseverations Execution time Completed Categories	Arango-Lasprilla et al. [77] Schretlen [78]
Inhibitory control	Classic stroop test	Number of stimuli words, letters and words/letters	Golden [79]

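### Optional improvement, not an error: Holm's step-down could replace Bonferroni at the same family-wise error and would never reject less

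*Protocol article*

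**What the plan says.** The Statistical analysis plan section tests the hypothesis with "Mixed Repeated Measures Analysis of Variance (ANOVA MR) with Bonferroni corrections", aimed at the comparison between groups. Time (pre-test, post-test, follow-up) is the within-subject factor and study arm the between-subject factor. The section does not say how many comparisons the correction covers, or whether it runs over time points within one ANOVA or across outcomes.

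Two other places bear on the point. Table 2 (Sample's size calculation) gives "α error confidence level 0,05" and "Sample power 0,95", with no adjustment for multiplicity, and arrives at 22 children per group. Table 4 (Primary outcome measures) lists seven primary variables, each with its own test and most with several scores. It is not described as the Bonferroni family.

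**The concern.** The correction method is named in the article, so it is a choice that can be reviewed now. For hypothesis tests in a family of two or more, Bonferroni is dominated: Holm makes the same promise about false positives, needs no further assumption and cannot lose a rejection. With a planned minimum of 44 children and a sample size worked out at an unadjusted 0.05, any correction is paid for out of the planned power, so it is sensible to use the version that costs least.

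The choice matters most when several effects are real. The Discussion says the trial should show how the training affects different executive processes differently. That is a question about which functions change, not only whether any does.

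**Working it through.** **1. The plan's own figure.** Table 2 gives alpha 0.05, power 0.95, two groups, three measures and an effect size of 0.25 to 0.5. Not stated, so assumed: the effect size is Cohen's f, the lower end (0.25) was used, the test is the group-by-time interaction, the correlation between measures is 0.5, and sphericity holds.

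- Noncentrality: λ = f² × N × m / (1 − ρ) = 0.0625 × 44 × 3 / 0.5 = 16.5
- Degrees of freedom: (2 − 1)(3 − 1) = 2 and (44 − 2)(3 − 1) = 84
- Power at N = 44 is 0.956. At N = 42 it is 0.946, which is below 0.95.

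So the stated total of 44 reproduces, for one test at an unadjusted 0.05. Choosing Holm or Bonferroni does not alter it.

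**2. Bonferroni does its job.** With m independent true nulls, family-wise error is 1 − (1 − 0.05/m)^m: 0.0492 for m = 3 and 0.0489 for m = 7. Unadjusted it would be 1 − 0.95^m: 0.143 and 0.302.

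**3. Why Holm cannot do worse.** Bonferroni compares every p-value with 0.05/m. Holm orders the p-values and compares the i-th smallest with 0.05/(m − i + 1), stopping at the first failure. The first threshold is 0.05/m and the later ones are larger, so every Bonferroni rejection is also a Holm rejection. In the simulations below no Bonferroni rejection was ever lost.

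**4. Bonferroni power per real effect.** A two-sided test with 80% unadjusted power has a mean shift of 1.960 + 0.842 = 2.80.

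- m = 3: critical value 2.394; power = Φ(2.80 − 2.394) = 0.66
- m = 7: critical value 2.690; power = Φ(2.80 − 2.690) = 0.54

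**5. Holm against Bonferroni.** Simulated equicorrelated normal statistics, two-sided family-wise 0.05. Families of 3 (the pairwise contrasts among three time points) and 7 (the primary tests) are assumptions. Average power per real effect, at 80% unadjusted power and correlation 0.3:

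| Family | Real effects | Bonferroni | Holm |
|---|---|---|---|
| 3 | 1 | 0.66 | 0.66 |
| 3 | 2 | 0.66 | 0.69 |
| 3 | 3 | 0.66 | 0.74 |
| 7 | 1 | 0.55 | 0.55 |
| 7 | 2 | 0.55 | 0.56 |
| 7 | 4 | 0.54 | 0.58 |
| 7 | 7 | 0.54 | 0.65 |

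(Bonferroni power for a family of 7 is 0.544 to 0.547 between runs; the difference is simulation error.)

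At the article's own 95% unadjusted power, with independent tests, the figures are 0.887 against 0.944 (3 of 3 real), 0.820 against 0.844 (3 of 7 real), 0.820 against 0.930 (7 of 7 real) and 0.820 against 0.821 (1 of 7 real).

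**6. What does not change.** The probability of at least one rejection is the same under both methods, because Holm's first step is the Bonferroni step. Family-wise error stayed at or below 0.05 for both.

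**The case against.** The strongest reply is that no defect has been shown. Bonferroni is standard, prespecified and conservative; no number or sentence in the article becomes wrong because of it; and the same remark could be made of any trial that uses it. That stands, and it is why this is an improvement and not a correction.

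A reader might go further and infer that Bonferroni brings no benefit and that the trial will miss real effects because of it. The article does not support either statement. Bonferroni gives matching simultaneous confidence intervals and one fixed threshold per comparison, which Holm does not give as directly. A gain arises only after another hypothesis in the same family has been rejected, and it is close to zero with one real effect. The largest gains above need every effect in the family to be real.

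It can also be said that the family is not stated. The wording may mean contrasts within each ANOVA, not a correction across the seven tests of Table 4. Because the Protocol design section applies the third measure to the experimental group only, few between-group contrasts might exist under that reading. This stands too. It limits the size of the gain, and it means the change should not presuppose a family across outcomes. It does not affect the direction, which holds for any family of two or more.

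**Conclusion.** The point holds as a low-priority, cheap improvement. For hypothesis tests, Holm offers the same family-wise error control as Bonferroni under any dependence and never rejects less. In the scenarios with several real effects at 80% unadjusted power and correlation 0.3, the gain in average power per real effect is about 3 points (2 of 3 real), 8 points (3 of 3), 4 points (4 of 7) and 11 points (7 of 7). It is about nil with a single real effect, and there is none if the family holds only one comparison.

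The family sizes, the correlation and the 80% figure are assumptions; the article fixes only alpha 0.05 and power 0.95. The comparison takes the p-values as valid and does not address the allocation of four whole school groups, so these are not estimates of this trial's actual power.

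**What to change.** In the Statistical analysis plan section, replace the Bonferroni correction with a Holm step-down correction, applied to whatever family of two or more comparisons Bonferroni was meant to cover, and report Holm-adjusted p-values. Make the change before outcome data are seen by arm.

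The cost is one phrase in the plan and one software option, with no extra children, assessments or assumptions. The one drawback is that simultaneous confidence intervals are less direct under Holm. Bonferroni intervals can be shown beside the Holm p-values, with a note that an interval may include zero for a comparison that Holm rejects.

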### Specific objectives and hypotheses

The following randomized controlled trial (RCT) protocol was designed to evaluate the effect of the COGNI-MACHINE computational thinking training program on the executive functions of fifth-grade children aged 9 to 11 years. This RCT has established the following working hypothesis:

There are significant differences in the evolution of executive functions and other cognitive processes, such as metacognition and attention, in fifth-grade children who receive training in computational thinking compared to those children who receive a conventional computer training program.

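### Seven primary tests carry 26 scores with no lead score and no correction stated across outcomes, while the sample size of 44 matches a single unadjusted 0.05 test

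*Protocol article*

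**What the plan says.** All references are to the protocol article.

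- **Primary outcomes.** The section on primary outcome measures opens with "To measure the executive functions of children we have selected neuropsychological tests with recognition and reliability studied". Table 4 then lists seven variables, one test each, and every test has two or more rating parameters. No parameter, composite or order of testing is singled out.
- **Hypothesis.** The section on objectives and hypotheses states one working hypothesis: "There are significant differences in the evolution of executive functions and other cognitive processes, such as metacognition and attention". Table 5 lists metacognition and attention as secondary.
- **Analysis.** The statistical analysis plan section announces a hypothesis test by mixed repeated-measures ANOVA "with Bonferroni corrections to look at the differences between groups". It gives neither the number of comparisons nor the family to which the correction belongs.
- **Sample size.** Table 2 gives "α error confidence level 0,05" and "Sample power 0,95", two groups ("1 experimental group and 1 TAU control group"), three measures ("Pretest, posttest, follow-up") and an effect size of 0.25 to 0.5. The text reports: "The G-Power projection suggested a group size of 22 children for a total sample of 44 children". The recruitment section expects to convene about 100 children, with dropout of around 15%.

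**The concern.** The trial has one hypothesis about executive functions and many scores that could be used to support it. The document does not say which score, or how many, must differ for the hypothesis to be confirmed. The only multiplicity device is attached to group differences. On its plain reading, it works inside each ANOVA and does nothing across the seven tests or their component scores.

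Two things are at stake. If nothing is corrected across outcomes, the error rate for a claim that training improves some executive function is well above 5%, and the choice of score to put forward can be made after the results are known. If the correction is meant to span outcomes, the alpha in Table 2 is not the alpha of the tests to be run, and the power quoted for 44 children is too favourable at the effect size that yields 44.

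**Working it through.** **1. Count of primary scores (Table 4).** Tower of London 4, Porteus maze 3, digits 6 (right answers in three orders, span in three orders), Corsi 2, picture span 2, M-WCST 6, Stroop 3. Sum: 4 + 3 + 6 + 2 + 2 + 6 + 3 = 26. Counting the digit right answers as one score and Stroop as one score gives 26 − 2 − 2 = 22.

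**2. Reproducing the sample size.** Inputs from Table 2: k = 2 groups, m = 3 measures, alpha 0.05, power 0.95. Assumptions, because the table does not state them: the effect size is Cohen's f, the test is the group-by-time interaction, the within-subject correlation ρ is 0.5, and epsilon is 1.

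- Noncentrality: λ = f²·N·m/(1 − ρ) = 0.0625 × 44 × 3/0.5 = 16.5
- Degrees of freedom: (k − 1)(m − 1) = 2 and (N − k)(m − 1) = 84
- Power from the noncentral F at alpha 0.05: 0.956. The smallest even N reaching 0.95 is 44.

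The stated figure is therefore reproduced by one test at an unadjusted 0.05. Other settings do not give 44: f = 0.5 needs 14, ρ = 0.3 needs 60, ρ = 0.7 needs 28, and the between-group main effect needs 142 (f = 0.25) or 38 (f = 0.5). The within-subject main effect gives the same 44 and is also a single test.

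**3. No correction across outcomes.** With q independent tests at 0.05, the chance of at least one false positive is 1 − 0.95^q:

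- q = 7: 1 − 0.698 = 0.302
- q = 22: 0.676
- q = 26: 1 − 0.264 = 0.736

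The scores come from the same children, and often from the same test, so independence is the upper end. Simulation with a common correlation between test statistics (200,000 draws; the correlations are assumptions) gives:

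| Correlation | 7 tests | 26 scores |
|---|---|---|
| 0 | 30% | 74% |
| 0.3 | 27% | 62% |
| 0.5 | 23% | 47% |
| 0.7 | 18% | 32% |

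**4. Bonferroni across outcomes.** Same model as step 2, f = 0.25, with alpha divided by the number of outcomes:

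| | Alpha per test | Power, N = 44 | N for 0.95 | Power, N = 84 |
|---|---|---|---|---|
| 1 test | 0.05 | 0.956 | 44 | above 0.99 |
| 7 tests | 0.05/7 = 0.00714 | 0.83 | 62 | 0.99 |
| 26 scores | 0.05/26 = 0.00192 | 0.70 | 72 | 0.98 |

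At f = 0.5, power at N = 44 stays above 0.99 in every row. N = 84 stands for 100 children less 15% (85), taken to the next even number down, with other exclusions ignored. All power figures ignore the clustering by school group, which is a separate matter.

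**The case against.** The best defence has four parts.

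- **The article condenses a fuller plan.** The correction family is the kind of detail such a plan may hold. This has some force: the scope of Bonferroni is unclear here rather than shown to be wrong. But the article itself fixes the list of primary scores, the correction method and the sample size, and these do not fit together. If a fuller plan extends the correction to outcomes, Table 2 no longer describes the tests.
- **Rating parameters are scoring components, not declared hypotheses.** This is fair, and 26 is the widest reading. Seven primary tests remain on the narrowest one, and nothing says how the components of a test are reduced to one result.
- **Forty-four is a floor, and about 100 children are expected.** This stands. At about 84 analysed, the power loss is gone, as it is at f = 0.5.
- **The bias table commits to reporting in line with the registered objectives.** That commitment helps against omission, but nothing in the article names a primary score.

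A reader might also infer that either reading of the correction contradicts a stated figure. It does not. Without correction across outcomes, 0.05 and 0.95 hold as per-test values, and the document states no family-wise rate. Nor do metacognition and attention become primary by appearing in the hypothesis; Table 5 makes them secondary.

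**Conclusion.** The confirmatory family is undefined, and the sample size takes no account of it. If outcomes are left uncorrected, the chance of at least one false-positive primary result is about 18–27% for seven tests and 32–62% for 26 scores, at assumed correlations of 0.7–0.3. That is more than three times 5% even at the low end. The values of 30% and 74% are ceilings under independence, so it would be wrong to conclude that a false positive is close to guaranteed.

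If outcomes are corrected by Bonferroni, power at the stated minimum is about 0.83 or 0.70 rather than 0.95. This rests on f = 0.25 with assumed ρ = 0.5 and epsilon 1, the combination that reproduces 44. It does not support a general claim that the trial is underpowered, because the shortfall vanishes at f = 0.5 or at about 84 children.

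Lower figures of 0.69 and 0.51 arise if only pre-test and post-test are compared at N = 44. They should not be charged to multiplicity alone, since dropping one measure already takes the uncorrected power to 0.90.

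**What to change.** Before outcome data are seen:

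1. Name one primary score for each of the seven tests in Table 4.
2. Apply Holm across the seven. State separately what the Bonferroni correction inside each ANOVA covers.
3. Treat the remaining scores as secondary or exploratory.
4. Align the working hypothesis with the primary outcomes. Metacognition and attention are already secondary in Table 5.
5. Restate Table 2 at the alpha actually used. At 0.05/7 and f = 0.25, power is 0.83 with 44 children, and 62 children are needed for 0.95. These are the values for Holm's first and strictest step.

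A single executive-function composite would also settle the multiplicity, but it would hide the differences between executive processes that the discussion section says the trial wants to recognise. One score per test serves that aim better.

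The cost is wording only, with no new data. The downside is a stricter threshold for each claim and a less favourable stated power at 44.
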